# Schema

**9 Gy in 3 fractions (experimental arm)**

**24 Gy in 12 fractions (SOC control arm)**

**Observation and Follow-up per protocol**

**Prescreen**

**Confirm eligibility through pathology and histology results and inclusion/exclusion criteria**

**1:1 Randomization**

**10 Gy in 5 fractions or 8 Gy in 2 fractions are acceptable alternatives at the physician discretion**

Duration of Participation: 24 months

Sample size: 102 patients

Subjects will be enrolled and followed on this study until 24 months after the completion of radiation treatment.

**List of Abbreviations**

| AE | Adverse Event/Adverse Experience |
| --- | --- |
| ISRT | Involved – site radiation therapy |
| CRF | Case Report Form |
| DSMB | Data and Safety Monitoring Board |
| SOC | Standard of Care |
| NHL | Non-Hodgkin’s Lymphoma |
| RT | Radiation Therapy |
| PI | Principal Investigator |
| IRB | Institutional Review Board |
| BED | Biological Effective Dose |
| OS | Overall survival |
| LC | Local control |
| ECOG | Eastern Cooperative Oncology Group |
| CTV | Clinical Tumor Volume |
| OTV | Optimization Target Volume |
| CT | Computed Tomography |
| PET | Positron Emission Tomography |
| QoL | Quality of Life |
| SOC | System Organ Class |
| MCCC | Mayo Clinic Cancer Center |
| IHC | Immunohistochemistry |
| FISH | Fluorescence in situ hybridization |

## **1.0 Background**

### Indolent Non-Hodgkin’s Lymphoma (NHL) constitutes around 40% of all NHL cases, with follicular lymphoma being the most common subtype [1]. Several studies have described the outcomes for patients with early-stage follicular lymphoma treated with RT alone, demonstrating 10-year progression-free survival (PFS) rates of approximately 50% and overall survival (OS) rates of 60% to 70% [2-4]. Various radiation techniques and doses were used during the different time periods covered in these studies. For example, patients received involved field radiation therapy (IFRT), extended-field radiation therapy (EFRT), total lymphoid irradiation (TLI), or sub-TLI (STLI) to doses of 35 Gy to 50 Gy at 1.5 Gy to 2.5 Gy per fraction. Relapses following radiation alone usually occurred at unirradiated sites [3]. Furthermore, a subsequent large study utilizing the Surveillance Epidemiology and End Results (SEER) registry found that including radiation in the treatment is associated with superior disease-specific and overall survival [5].

### Studies evaluating the use of RT in patients with early-stage indolent lymphoma have typically used radiation doses between 20 Gy–50 Gy. Although retrospective studies have demonstrated that lower radiation doses appeared to be as effective as higher doses, a recent phase III randomized study from the United Kingdom tested the results of 24 Gy versus 40 Gy–45 Gy, and showed similar overall response rate, local control rate, PFS and OS [6]. Thus, lower doses of 24 Gy to 30 Gy are generally preferred due to the anticipated lower risk of radiation-induced acute and late toxicity. Owing to improvements in staging, modern technology, use of image guidance and concern for radiation toxicity, treatment fields have also decreased from TLI, to extended field radiation (EFRT), to IFRT, and most recently to involved site radiation (ISRT) / involved node radiation (INRT) as it was shown to be equally effective and less toxic [7].

### Given the extreme radiosensitivity of indolent lymphoma and efficacy of lower doses of radiation, retrospective studies showed that 4 Gy in 2 fractions, specifically for orbital indolent lymphoma, achieved high response rate with minimal toxic effects, much shorter treatment course and lower cost [8]. Unfortunately, prospective attempts to replicate this reduction of RT dose for follicular and marginal zone NHL showed inferior disease control [9]. The FoRT study randomized patients with indolent lymphoma at 2 Gy/fraction to either 24 Gy or 4 Gy total radiation dose, which translates to a biologically effective dose (BED) of 29 Gy and 5 Gy when using an alpha/beta ratio of 10. The 2-year local progression-free rate was 94.1% after 24 Gy and 79.8% after 4 Gy demonstrating superiority in the 24 Gy arm. However, toxicity rates were significantly worse with 24 Gy compared to 4 Gy (Grade 2+ acute toxicity: 34% vs. 10%) [9]. While 24 Gy remains the standard of care based on disease control, many radiation oncologists continue to use 4 Gy as initially treatment and will use 20-24 Gy for those patients who develop a local relapse after 4 Gy without compromising overall survival. .

### This leaves us with important unanswered questions. 1) Can we find a more optimal intermediate dose between 4 Gy and 24 Gy that is similarly effective with respect to disease control as 24 Gy but has shorter treatment course, lower clinical and financial toxicity, and less financial health care expenditure? 2) Can we personalize RT for patients with indolent NHL by identifying prognostic predictors of local control and radio-resistance?

### Currently, risk stratification for indolent lymphoma includes the FLIPI and FLIPI 2, which use traditional prognostic factors based on blood tests (LDH, beta microglobulin) and CT imaging for size and sites involved, but do not take into consideration more contemporary techniques, such as functional imaging segmentation values and molecular classification. Recent studies revealed that functional imaging 18-fluoro-deoxyglucose (FDG) metabolic tumor volume (MTV) and total lesions glycolysis (TLG) serve as prognostic factors in indolent lymphoma. High MTV and TLG were associated with shorter time to treatment initiation and worse outcome [10-12]. These studies, however, focused on outcomes following systemic therapy and we do not have data on impact of functional imaging for patients with indolent lymphoma undergoing radiotherapy. Furthermore, studies have shown worse survival in patients with indolent lymphoma who have increased expression of TP53, MYC, BCL2, and FOXP1 [13-15].

### To date, we lack the optimal intermediate RT dose and the multidisciplinary approach that utilizes the clinical, molecular, and radiological features for indolent lymphoma to personalize radiotherapy treatment.

### Therefore, the purpose of this project is to evaluate reduction of radiotherapy dose for patients with indolent NHL by conducting a prospective randomized phase 2 study comparing reduced dose hypofractionated ISRT of 9 Gy delivered over 3 fractions (BED 12 Gy) to standard of care 24 Gy delivered over 12 fractions (BED 29 Gy), while simultaneously evaluating prognostic value of pre-radiation functional imaging parameters and molecular markers to predict treatment response and failure.

## **2.0 Goals**

### 2.1 Primary Goal

The planned study is a randomized Phase 2 trial with the primary goal to show that the experimental arm (9 Gy in 3 fractions, 8 Gy in 2 fractions, or 10 Gy in 5 fractions) has significantly reduced acute toxicity (grade ≥ 2 adverse events at least possibly related to radiation treatment within 14 days after the end of radiation treatment (according to CTCAE v5.0)) compared to 24 Gy in 12 fractions.

### 2.2 Secondary Goals

The secondary objectives of the study are to evaluate:

- Patient Reported Quality of life [timeframe: 7 days after radiation treatment end date]
- Response rate [timeframe: at 3 months (+/- 14 days) post radiation treatment start date]
- Local control rate [timeframe: up to 24 months after the completion of radiation treatment]
- Relapse-free survival [timeframe: up to 24 months after completion of radiation treatment]

2.3 Exploratory Goals

- Financial toxicity will be assessed at the end of radiation treatment.
- Financial Health Care Expenditure will be assessed at the end of radiation treatment
- Late Toxicity. Late adverse events will be assessed at 3 months post radiation treatment. Toxicity refers to those adverse events that are possibly related to radiation treatment.

2.4 Correlative Research

2.4.1 Biopsies of enrolled patients will be evaluated for pathological assessment of cellular and genetic mutations to correlate them with disease local relapse and radiation resistance. This includes:

- TP53 gene alteration by Fluorescence in situ hybridization (FISH)
- Expression of TP53, MYC and proliferation index (Ki-67) by immunohistochemistry stain (IHC)

#### 2.4.2 Patients will have their baseline PET/CT scan undergo auto-segmentation to calculate the functional imaging 18-fluoro-deoxyglucose (FDG) metabolic tumor volume (MTV), total lesions glycolysis (TLG) and maximum standardized uptake volume (SUVmax) of the sites to be treated with ISRT using MIMvista platform to correlate it with disease local relapse and treatment response.

## **3.0 Eligibility**

### 3.1 Registration – Inclusion Criteria

#### 3.1.1 Age ≥18 years

#### 3.1.2 Histological confirmation of indolent B-cell lymphoma that can include any of the following:

#### Follicular lymphoma (grade 1 or 2 or 3A)

#### Marginal zone lymphoma (Nodal or extranodal)

Follicle center lymphoma

#### 3.1.3 Any stage disease

#### 3.1.4 Initial, refractory, or relapsed disease. If relapse involves the site to be treated there must be evidence of disease progression

#### 3.1.5 ECOG Performance Status (PS) ≤3 (Appendix I)

#### 3.1.6 Negative pregnancy test done ≤7 days prior to registration, for persons of childbearing potential only

#### 3.1.7 Provide written informed consent

#### 3.1.8 Ability to complete questionnaire(s) by themselves

#### 3.1.9 Willing to return to enrolling institution for follow-up (during the Active Monitoring Phase of the study). Virtual visits can also be considered as an option for applicable items

3.1.10 Confirmation from radiation oncologist of suitability to participate in study

### 3.2 Registration – Exclusion Criteria

#### 3.2.1 Any of the following:

#### Pregnant women

#### Nursing women

#### Men or women of childbearing potential who are unwilling to employ adequate contraception

#### 3.2.2 T-cell lymphoma

#### 3.2.3 Small and chronic lymphocytic lymphoma

#### 3.2.4 Grade 3B follicular lymphoma

##

## **4.0 Test Schedule**

|  |  | **Active Monitoring Phase** | | | **Clinical Follow-Up** | | |
| --- | --- | --- | --- | --- | --- | --- | --- |
| **Tests and procedures** | ***≤ 45 days prior to registration*** | ***End of Treatment*** | ***Day 7***  ***post-ISRT*** | ***Day 14***  ***post-ISRT*** | ***3 Months***  ***post-RT^1^*** | ***6 Months***  ***post-RT*** | ***Every clinically indicated follow-up***  ***(q 6 months)^1^*** |
| Window |  | ±1 day | ±2 days | ±2 days | ±14 days | ±30 days | ±30 days |
| History and exam, PS^2^ | X |  |  |  | X | X | X |
| Radiation Oncology consult^2^ | X |  |  |  |  |  |  |
| Adverse Event assessment^3^ | X | X | X | X | X |  |  |
| Pregnancy test^2,^4 | X |  |  |  |  |  |  |
| Hematology group: CBC with 5-part differential  (HgB, WBC, PLT, LDH)^2^ | X |  |  |  |  |  |  |
| PET/CT ^2^ | X  (90 days) |  |  |  | X  (strongly consider, unless FDG negative at baseline) | X* | X* |
| CT Chest/Abdomen/Pelvis +/- Neck^2, 7^ |  |  |  |  | X  (if PET not done) | X* | X* |
| Endoscopy with gastric biopsy (only if gastric lymphoma)^2^ | X  (***≤*** 90 days) |  |  |  | X^6^ | X** |  |
| Patient Reported Outcomes (Appendix II: FACIT-Fatigue)^3^ | X | X | X |  | X |  |  |
| Financial Toxicity Questionnaire  (Appendix II: COST-FACIT)^3^ |  | X |  |  |  |  |  |
| Optional Research,  tissue specimen5^,R^ |  | X |  |  |  |  |  |

Radiation treatment (RT) = 3 vs. 12 fractions (5 days vs. 16 days ±2 days)

^1^ Follow-up assessments will be completed as per clinician’s discretion.

^2^ Standard of care

^3^ Research non-billable

^4^ For persons of childbearing potential only. Must be done ≤7 days prior to registration.

^5^ Historic tissue specimen may be pulled and used for analysis by end of study.

^6^ +/- 30 days

^7^ CT and/or PET should not be mandated for patients with primary cutaneous lymphoma where physical exam is used for evaluation of treatment response..

^R^ Research funded

* CT chest/abdomen/pelvis +/- neck or PET/CT or PET/MRI ok at these time points

** If 3 month biopsy was positive

Event monitoring is the period when the participant is no longer following the protocol test schedule due to disease progression and/or the patient was started on a new non-study anti-cancer treatment. During Event Monitoring, the data collection schedule is dictated by the protocol, but the visit schedule is determined by clinical practice at each participating site. During the Event Monitoring Phase of the study, the participant is being monitored for key study events such as new non-study anti-cancer treatments given, new primaries, and death. Samples from biospecimens collected in the course of clinical care may be requested but cannot be required of the participant.

##

## **5.0** **Stratification Factors OR Grouping Factors**

Stage I/II vs. Stage III/IV/relapse/refractory

Enrollment site (FL, AZ, MN)

## **6.0 Registration/Randomization Procedures**

### 6.1 Registration (Step 1)

#### 6.1.1 Registering a Patient

To register a patient, access the Mayo Clinic Research Registration Application at <https://registration.mayo.edu>. The registration/ randomization application is available 24 hours a day, 7 days a week. Back up and/or system support contact information is available on the website. If unable to access the website, email Research Registration Office at [[contact]](mailto:[contact]) between the hours of 8 a.m. and 4:30 p.m. Central Time (Monday through Friday).

The instructions for the registration/randomization application are available on the Mayo Clinic Office of Clinical Trials web page (<https://www.mayo.edu/research/centers-programs/center-clinical-translational-science/offices/office-of-clinical-trials/research-registration-application>) and detail the process for completing and confirming patient registration. Prior to initiation of protocol treatment, this process must be completed in its entirety and an MCCC subject ID number must be available as noted in the instructions. It is the responsibility of the individual registering the patient to confirm the process has been successfully completed prior to release of the study agent. Patient registration via the registration/randomization application can be confirmed in any of the following ways:

- Contact the Research Registration Office at [[contact]](mailto:[contact]). If the patient was fully registered, the Research Registration Office staff can access the information from the centralized database and confirm the registration.
- Refer to the Research Registration Application training course on the Mayo Clinic Office of Clinical Trials webpage (link above) for instructions on viewing the patient’s registration confirmation.

### 6.2 Randomization Procedures

#### 6.2.1 The factors defined in **Section 5.0** will be used as stratification factors.

#### 6.2.2 After the patient has been registered into the study, the values of the stratification factors will be recorded, and the patient will be assigned to one of the following treatment groups using the Pocock and Simon dynamic allocation procedure, which balances the marginal distributions of the stratification factors between the treatment groups (Pocock and Simon 1975).

- Arm 1: The prescription dose will be 9 Gy delivered in 3 fractions of 3 Gy per fraction or 8 Gy delivered in 2 fractions of 4 Gy per fraction . In some cases, the investigator can use 10 Gy delivered in 5 fractions (stomach/orbit/other at treating MD’s discretion).
- Arm 2: The prescription dose will be 24 Gy delivered in 12 fractions of 2 Gy per fraction.

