7.1.2 Treatment planning and delivery

Treatment can be delivered using photons, protons, or electrons at the treating physician’s discretion. When treating with photons; 3D-conformal radiotherapy (3D-CRT), intensity modulated radiotherapy (IMRT), or volumetric arc radiotherapy (VMAT) are all allowed.

Arm 1: The prescription dose will be 9 Gy delivered in 3 fractions of 3 Gy per fraction or 8 Gy delivered in 2 fractions of 4 Gy per fraction. Treatment will be delivered one fraction a day except on weekends and holidays. Note that at the treating physician’s discretion (such as for gastric, dural, orbital, other lymphoma), 10 Gy in 5 fractions is allowed as an alternative ifractionation.

Arm 2: The prescription dose will be 24 Gy delivered in 12 fractions of 2 Gy per fraction. Treatment will be delivered one fraction a day except on weekends and holidays.

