16.4.1.1 TP53 gene alteration by Fluorescence in situ hybridization (FISH)

16.4.1.2 Expression of TP53, MYC and proliferation index (Ki-67) by immunohistochemistry stain (IHC)

16.4.2 Baseline PET/CT scan of patients will be sent to MIMvista to undergo autosegmentation to calculate the MTV, TLG and SUVmax of their disease to correlate it with disease local relapse and treatment response.

16.4.3 Financial toxicity: financial side effects induced by cancer treatment that will be assessed by a modified COST-FACIT questionnaire as outlined in section 4.0 and 7.0.

16.4.4 Financial health care expenditure reflects the costs spent on health care and related activities attributable to this cancer treatment and will be assessed as outlined in section 4.0 and 7.0.

16.4.5 Sensitivity analysis to assess differences in the different radiation dose regimens in the experimental treatment arm.

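### The exploratory regimen comparison within Arm 1 (16.4.5) can only be descriptive; recording each patient's intended Arm 1 regimen before allocation would cheaply add a randomised comparison

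*Protocol*

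**What the plan says.** Arm 1 contains three regimens. The Schema shows 9 Gy in 3 fractions and adds that "10 Gy in 5 fractions or 8 Gy in 2 fractions are acceptable alternatives at the physician discretion". Section 6.2.2 puts 9 Gy/3 and 8 Gy/2 side by side without a criterion for choosing between them, and then says: "In some cases, the investigator can use 10 Gy delivered in 5 fractions (stomach/orbit/other at treating" physician's discretion). Section 7.1.2 repeats this with a slightly longer list of sites: "such as for gastric, dural, orbital, other lymphoma), 10 Gy in 5 fractions is allowed as an alternative".

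On what is captured before allocation, Section 6.2.2 says that "the values of the stratification factors will be recorded, and the patient will be assigned to one of the following treatment groups". Section 5.0 gives two factors: "Stage I/II vs. Stage III/IV/relapse/refractory" and enrollment site (Florida, Arizona, Minnesota). The checks in Section 6.3 and the descriptive factors in Section 12.0 do not mention an intended regimen. The nearest descriptor of anatomy in Section 12.0 is extranodal, yes or no.

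Among the exploratory endpoints, Section 16.4.5 lists: "Sensitivity analysis to assess differences in the different radiation dose regimens in the experimental treatment arm". It says nothing further on method and claims no causal reading.

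Treated site itself can be recovered in both arms. Section 2.4.2 segments the baseline PET/CT "of the sites to be treated with ISRT using MIMvista platform", Section 4.0 schedules "Endoscopy with gastric biopsy (only if gastric lymphoma"), and Section 11.3 classifies failures against the treatment plan.

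**The concern.** Randomisation protects the comparison of Arm 1 as a whole with Arm 2. It does not protect a comparison between regimens inside Arm 1, because a physician chose who received which. For 10 Gy/5 the stated reasons are anatomical (gastric, dural, orbital). The solicited events in Section 10.2.1.2 include site-dependent ones such as dry eye, oral mucositis and nausea. A regimen difference and a site difference would look the same.

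A better question for the same exploratory item is how Arm 1 compares with 24 Gy among patients for whom the physician would have used a given regimen. That comparison is randomised, but only if the intended regimen is known in both arms. In Arm 1 the regimen given becomes known after allocation; in Arm 2 nothing reveals it. An analysis plan written later can adjust for treated site, but it cannot supply a choice that nobody asked for before allocation.

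What is at stake is modest but practical. A favourable result is meant to support future trials (16.5.1.1), and the protocol already separates regimens in its stopping rule (16.7.2) and names 10 Gy/5 as the fallback (8.0). Whoever designs the next trial will ask which regimen the result supports.

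**Working it through.** **The plan's own figure.** Section 16.5.4 states 80% power with 51 per arm, 31% v 10%, two-sided 0.10. Exact enumeration gives 79.1% for the continuity-corrected chi-squared test and 85.8% for the uncorrected one. The figure is sound, and nothing below alters it.

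**What could define a matching group in Arm 2.**

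| Arm 1 regimen | Basis of choice in the protocol | Counterpart in Arm 2 without the field |
| --- | --- | --- |
| 10 Gy/5 | discretion, linked to gastric, orbital, dural or other site | treated site, in part; the 'other' cases are missed |
| 8 Gy/2 v 9 Gy/3 | discretion, no criterion given | none |

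**Could site alone create a regimen difference?** From the protocol: 31%, 10% and 51 per arm. Assumed: the share s steered to 10 Gy/5, and the risk p1 of those patients under 24 Gy. Every regimen is given the same relative effect, RR = 0.10/0.31 = 0.3226, so any difference found is false.

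- Risk elsewhere: p0 = (0.31 - s × p1)/(1 - s)
- False within-Arm-1 difference: RR × (p1 - p0)

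| s | p1 | p0 | False difference (points) |
| --- | --- | --- | --- |
| 0.20 | 0.20 | 0.3375 | -4.4 |
| 0.20 | 0.45 | 0.2750 | +5.6 |
| 0.20 | 0.60 | 0.2375 | +11.7 |
| 0.30 | 0.20 | 0.3571 | -5.1 |
| 0.30 | 0.45 | 0.2500 | +6.5 |
| 0.30 | 0.60 | 0.1857 | +13.4 |

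**Noise of that contrast**, with 10% in both groups. A 20% or 30% share of 51 is about 10 v 41 or 15 v 36.

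- 1.96 × √(0.09 × (1/10 + 1/41)) = 0.207
- 1.96 × √(0.09 × (1/15 + 1/36)) = 0.181

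Every false difference in the table is smaller than the matching half-width. For 8 Gy/2 v 9 Gy/3 the protocol gives no basis for a bias figure, so none is offered.

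**What the field would buy.** For Arm 1 v Arm 2 within an intended-regimen group of n per arm at 31% v 10%, the 95% half-width is 1.96 × √((0.31 × 0.69 + 0.10 × 0.90)/n) = 1.96 × √(0.3039/n). Power is by exact enumeration of the uncorrected chi-squared test at two-sided 0.10. Group sizes are assumed, as the protocol gives no split.

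| n per arm | Example | Half-width (points) | Power |
| --- | --- | --- | --- |
| 10 | intended 10 Gy/5, 20% share | 34 | 30% |
| 15 | intended 10 Gy/5, 30% share | 28 | 45% |
| 20 | 9 Gy/3 alone, if 41 split about evenly | 24 | 52% |
| 36 | 8 and 9 Gy pooled, 30% share to 10 Gy/5 | 18 | 73% |
| 41 | 8 and 9 Gy pooled, 20% share to 10 Gy/5 | 17 | 79% |
| 51 | whole trial | 15 | 86% |

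The better rows pool 8 and 9 Gy and come close to the whole trial, so they add little to the primary comparison. The useful single-regimen row is intended 9 Gy/3, whose precision depends on how often physicians prefer it.

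**Comparing effects between groups** is weaker still: 1.96 × √(0.3039 × (1/10 + 1/41)) = 0.381, and 0.332 with 15 and 36.

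**The case against.** The strongest reply is that the protocol states nothing false. Section 16.4.5 is exploratory, claims no randomised reading and promises no effect against 24 Gy by intended regimen. The added field serves a new question and does not repair the within-arm contrast, which stays selected however early the regimen is declared. All of that stands, and it is why this is an improvement rather than an error.

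Second, a reader might infer that no randomised estimate by regimen can exist. The documents do not support that. Section 6.2.2 says what is recorded, not that nothing else is. The registration instructions (6.1.1) and data forms (18.1) lie outside the protocol, so a screen not shown may already collect the intended regimen. Grouping both arms by baseline treated site also respects randomisation and covers much of 10 Gy/5. It leaves out the 'other' cases and cannot separate 8 Gy/2 from 9 Gy/3.

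Third, a reader might infer that the regimen results will be badly biased. The working does not show this: the illustrated differences rest on assumed risks and lie within noise. A larger bias would arise from setting one Arm 1 subset against all of Arm 2, but the protocol does not plan that comparison.

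Fourth, a single field is not quite trivial. Section 12.0 allows more than two treated sites, and Section 8.0 could move all of Arm 1 to 10 Gy/5, after which the field would carry no information. Both need a line of instruction.

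**Conclusion.** This is a cheap improvement to an exploratory item. The within-Arm-1 comparison in 16.4.5 is physician-selected and, for 10 Gy/5, linked to treated site, so it can only be descriptive. That follows directly from the Schema, 6.2.2 and 7.1.2. The protocol does not state that the intended regimen is recorded before allocation. If no unseen form collects it, Arm 2 has no counterpart group by intended regimen, apart from the partial substitute of treated site for 10 Gy/5.

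The size is limited. Site alone might shift the 10 Gy/5 contrast by about -5 to +13 points under the assumptions shown, which the trial could not distinguish from chance. Randomised estimates by intended regimen would be free of that selection but wide: about 24 points either side at 20 per arm and 34 at 10 per arm. A reader might take the point to weaken the primary result. It does not: the pooled Arm 1 v Arm 2 comparison and the decision rule in 16.5.1.1 do not depend on which regimen was chosen.

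**What to change.** - In 6.2.2, require that before assignment, for every patient, the Arm 1 regimen the physician would use is recorded. State how a patient with several treated sites is classified, and that the field lapses if Section 8.0 converts Arm 1 to 10 Gy/5. If the registration screen already asks for it, say so.
- In 16.4.5, report the Arm 1 v Arm 2 risk difference and relative risk by intended regimen, chiefly for intended 9 Gy/3, whatever regimen was then given. Use score 95% intervals as in 16.6.1.1 and mark the results exploratory and imprecise.
- For any patients enrolled before the field exists, group both arms by treated site from the treatment plan.
- Label contrasts between regimens within Arm 1, and comparisons of effects across intended-regimen groups, as descriptive, because site and regimen cannot be separated.

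The cost is one registration field and a rewording of 16.4.5. The downsides are small groups, a missing field for patients already enrolled, and only a partial substitute for them. Sample size, primary analysis and decision rule stay as they are.
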